##### Passive risk-taking

We will measure participants' tendency of passive risk-taking using the Passive Risk-Taking Scale (Keinan and Bereby-Meyer, 2012). While risk mostly occurs during action, passive risk-taking can influence potential losses due to inaction. This test contains three subscales regarding risks that involve resources, medical issues and ethical issues. It has 25 items in total and uses a Likert-type rating scale in which participants will rate how likely they will act according to the statements (i.e., “Get vaccinated for the flu in the winter”). This scale has a high internal validity and reliability (α = 0.82).

##### Elaboration of potential outcomes

The Elaboration on Potential Outcomes (EPO, Nenkov et al., 2008) measure will be used to assess participants' tendencies to generate and evaluate possible positive and negative consequences of their behavior, and measure their attitudes toward risk-taking. The instrument consists of 13 items, which are divided into three subscales with high internal consistency: generation/evaluation (e.g., “I try to anticipate as many consequences of my actions as I can”; α = 0.88), positive outcome focus (e.g., “I keep a positive attitude that things always turn out all right.”; α = 0.87), and negative outcome focus (“I am often afraid that things might turn out badly”; α = 0.87). The measure was also found to have strong factor structure, high test-retest reliability and high predictive validity (construct of EPO is an important determinant of self-regulation).

#### Translation and the pilot studies

Every text in the study will be presented to participants in their own language: Traditional Chinese, Finnish, German, Spanish, Slovenian, Serbian, and Dutch. The questionnaires are constructed and written in English, then two separate translators for each of the seven languages translated (e.g., English to German) the battery. After that, back translations were compared with the original battery. The translators are native to the language they are translating to, and have at least a C1 level in the Common European Framework of Reference for Languages in said language. The process will be repeated until a third independent translator, native in English, considers that the original text and the back translation are equal in meaning.

The first pilot study will be conducted with the aim of testing the questionnaire framework and interaction with participant, and also to test psychometric characteristics of items and to eliminate those invalid. The battery is administered online in an English-speaking area, such as the UK, with a bigger sample that allows enough variability in the responses to the items to explore their functioning (i.e., 100 participants). We will assess item and subscale reliability and validity, and perform a factorial analysis.

Once the translation is prepared, we will conduct the second pilot study. The aim is to identify problems with items that may have appeared through the translation process. For example, items could be potentially ambiguous, unclear or misleading for participants (Ziegler et al., 2015). The battery will be administered to ~15 parents from each country and their responses will serve to adapt the problematic items and improve the battery.

### Proposed analysis

We will use statistical software (Matlab, R) for data analysis. We will analyse samples from each country separately because the differences in terms of language, legal framework in relation to vaccines, demographical characteristics and representativeness make the comparability between the different samples, and thus, their conjugate analysis, difficult (Ember et al., 1998).

For each sample, a factor analysis will be conducted to reduce the number of factors and control for interrelatedness of the variables. Two clusters of variables will be included: demographics (age, education level, number of children, mean age of children), and vaccine-related decision constructs (scores on scales on vaccination, vaccine hesitancy, perceived freedom of the decision, choice overload, actively open-minded thinking, trust toward authorities, availability of relevant information, perceived scientific consensus on vaccination, subjective estimation of percentage of children vaccinated on the country, perceived social consensus on vaccination, risk taking, and elaboration of potential outcomes). We expect the factor structure of each sample to be similar. With the reduced number of factors, a multivariate linear regression analysis will be conducted and the predictive power will be tested. The aforementioned factors will serve as predictors, and the parental intention to vaccinate (“I plan to vaccinate my child in accordance to the official vaccination schedule of my country”) will serve as criterion. All variables mentioned will also be included in a multivariate analysis of variance to see if there are differences between them depending on the level of adherence (total adherence, not completely total adherence, no adherence at all) to the official vaccination schedule of their children. We will test the proposed model of mediation (Figure 1) using regression analysis and compare it to a more complicated model with involvement as an additional factor.

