## Introduction

One of the greatest public health challenges today concerns suboptimal vaccine uptake rates. In 2017, measles affected 21,315 people and caused 35 deaths, according to WHO's press release from 19 February 2018. “The surge in measles cases in 2017 included large outbreaks in 15 of the 53 countries in the (European) region. The highest numbers of affected people were reported in Romania (5,562), Italy (5,006), and Ukraine (4,767)” (World Health Organization, 2018). Greece, Germany, Serbia, the United Kingdom, Spain, Bulgaria, and France also experienced large outbreaks (World Health Organization, 2018). This is a result of suboptimal vaccine rates (World Health Organization, 2017a): in many areas, the coverage rates of common vaccines have decreased below 95% that is postulated as the minimum to herd immunity, the effective halting of the spread of measles and other vaccine-preventable diseases.

While some children cannot be vaccinated for medical reasons and in some areas vaccines are not readily available, a growing number of children are not vaccinated or are vaccinated late largely due to their parents' conscious decision (Pearce et al., 2008). The resistance to be vaccinated or to delay vaccinations despite having available vaccinating services, has been dubbed vaccine hesitancy (Luthy et al., 2009; Gowda and Dempsey, 2013; World Health Organization, 2014). Numerous interventions have been introduced to combat vaccine hesitancy, but many are lacking in success (Sadaf et al., 2013; Dubé et al., 2014; Pluviano et al., 2017). To better combat vaccine hesitancy and optimize interventions, factors associated with parents' decisions on vaccination need to be identified and investigated.

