### Methods

#### Design, sample, and procedure

Participants will be parents or primary caregivers of children that are of the recommended age to receive vaccinations from their corresponding countries across Europe and Asia (i.e., Finland, Germany, Hong Kong, the Netherlands, Serbia, Slovenia, and Spain). Participants must be (a) over 18 years old, and (b) a parent or care taker of at least one child under the age of 12 years (Salmon et al., 2005; Jones et al., 2012).

The sample size will be a minimum of 222 participants per country, based on a power analysis for an effect size of 0.15, and 20 predictors in a linear multiple regression model. The final sample size will not have a difference greater than 10% between each country. To make sure that there aren't any significant differences between the sample sizes of the different countries, if the sample of any country exceeds 10% of the mean, some participants will be randomly discarded until the criterion is met.

The questionnaire is programmed in JavaScript and will be administered online. To take part in the study, participants will need an electronic device with access to internet. The link with an unbiased invitation letter will be posted on different social media platforms, forums and websites, targeting a wide range of parents from the entire vaccine-hesitancy spectrum. Once the link is opened, participants will first be given a brief introduction of the study. Participants will then read and sign an informed consent, which states they are able to halt and withdraw from the study at any moment without providing a reason, and that they agree for their anonymized data to be analyzed for future publications. Participants will be asked to compose a unique identification code (consisting of their parents' initials, and month of birth), which will be used to identify their data if they decide to withdraw their data after completing the study. After that, participants will be asked to provide their demographic information and complete a battery of vaccination- and decision-making-related questions, with a total of 115 items (the complete battery is in Appendix 1). Participants will be able to leave items unanswered. The study will take ~25 min to complete, but will vary depending on participants' speed of responding. This procedure was ethically approved by the Institutional Review Board of the Faculty of Philosophy at the University of Belgrade.

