##### Vaccine hesitancy

To identify vaccine hesitant parents, we will use Opel et al's. (2011) revised version of Parent Attitudes about Childhood Vaccines (PACV). The measure consists of 15 items, which are divided into three sub-domain scales: Safety and efficacy (α = 0.74), General attitudes (α = 0.84) and Behavior (α = 0.74). The measure has high internal and construct validity, and shows a statistically significant linear association between parents' total score on the 15-item PACV and their child's vaccination status (Opel et al., 2011). To increase the consistency of type of response along the scale and increase the sensitivity of the measure, we transformed some of the multiple-choice items to 7-point Likert type scales, in which each of the extremes represent the options that were included in the original scales. Finally, the item number 15 that referred to parents' trust toward their child's doctor, have been moved to the Trust Toward Authorities Scale (see Appendix 1 for detailed description of the battery).

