**Figure 1 F1:**
[figure not shown]
Proposed model of the factors of the intention to vaccinate.

For the open-ended question in which parents will detail their reasons for not absolutely adhering to the official vaccination schedule in their country, we will perform a qualitative analysis. After a pre-analysis, we will categorize answers based on the main reasons provided (e.g., medical reasons, considering vaccination risky etc.), and report the frequencies for each of them.

We will also check, using ANOVA, if there are differences in dependent variable (i.e., intention to vaccinate) according to participants' gender, marital status, while also considering whether vaccination is mandatory in their country of residence.

To check if the sources of information parents use to make vaccine-related decisions affect their intention to vaccinate, we will use ANOVA and *post-hoc* analysis.

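### The Study 1 adherence MANOVA mixes missed vaccination for medical or access reasons with missed vaccination by parental decision, and the collected reasons are not used to separate them

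*Protocol article*

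**What the plan says.** In the protocol article, Study 1, Proposed analysis, every listed demographic and psychological variable enters a MANOVA, and the parents are compared "depending on the level of adherence (total adherence, not completely total adherence, no adherence at all) to the official vaccination schedule of their children". The grouping variable has three levels, and none of them depends on why the schedule was not followed.

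The end of the same section deals with the reasons. "For the open-ended question in which parents will detail their reasons for not absolutely adhering to the official vaccination schedule in their country", a qualitative analysis is planned: "we will categorize answers based on the main reasons provided (e.g., medical reasons, considering vaccination risky etc.), and report the frequencies for each of them". No other use of the coded reasons is stated.

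The Introduction separates the causes of missed vaccination. Its sentence opens "While some children cannot be vaccinated for medical reasons and in some areas vaccines are not readily available" and then sets these cases against the growing number of children who miss vaccines mainly because their parents so decide. It goes on: "The resistance to be vaccinated or to delay vaccinations despite having available vaccinating services, has been dubbed vaccine hesitancy".

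Eligibility (Study 1, Design, sample, and procedure) requires an adult who is "a parent or care taker of at least one child under the age of 12 years". Families whose child has a contraindication or no access to a vaccine are not excluded.

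**The concern.** The Introduction distinguishes two kinds of missed vaccination, and the MANOVA joins them again. A parent who favours vaccination but whose child was delayed by illness, a contraindication or lack of supply would be analysed beside a parent who declined. Such parents would be expected to resemble adherent parents on trust, perceived consensus and hesitancy, and so to pull the non-adherent means toward the adherent mean.

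What is at stake is interpretation. Study 1, Anticipated results, expects to confirm which factors reinforce delaying or omitting childhood vaccination, and the Joint discussion repeats that aim. Within Proposed analysis, the adherence MANOVA is the comparison of these factors by the child's reported schedule status. A delay with a medical or supply cause is not a decision those factors could explain. With the causes mixed, a true difference can be missed, and a difference that is found cannot be assigned to parental decisions alone.

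**Working it through.** **The plan's own figure.** The only size calculation in Study 1 is for the multiple regression: 222 per country, effect size 0.15, 20 predictors. With 0.15 read as f², a noncentral F test (λ = f²N, df 20 and N − 21) and an assumed two-sided alpha of 0.05, power of 0.80, 0.90 and 0.95 needs N = 157, 191 and 222. The stated 222 is therefore reproduced at 95% power. It does not bear on this point beyond supplying a sample size; the MANOVA has no size calculation of its own.

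**What the text fixes.**
- Grouping: level of adherence only (Study 1, Proposed analysis).
- Reasons: collected in an open question, with medical reasons and perceived riskiness named as separate example categories, then counted (same section).
- Supply: named in the Introduction but not among the examples for coding; it would fall under the open end of that list.
- Link between reasons and groups: none stated.

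**Size of the dilution.** Let p be the share of a non-adherent group that deviated for medical or access reasons, and assume these parents have the same mean as adherent parents. With true standardised difference d:

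observed difference = (1 − p) × d

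For an assumed d = 0.50: 0.90 × 0.50 = 0.45; 0.75 × 0.50 = 0.375; 0.50 × 0.50 = 0.25.

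**Does separating the cases help, given that the group gets smaller?** The illustration uses one outcome, a two-group normal approximation and two-sided alpha 0.05. N = 222 comes from the protocol. The assumption that 20% are non-adherent gives n₁ = 44.4 and n₀ = 177.6.

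- Mixed: variance of the non-adherent group s² = 1 + p(1 − p)d²; SE = √(1/n₀ + s²/n₁); power = Φ[(1 − p)d/SE − 1.960].
- Separated: n₁′ = n₁(1 − p); SE′ = √(1/n₀ + 1/n₁′); power = Φ[d/SE′ − 1.960].

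For p = 0.25:
- Mixed: s² = 1 + 0.1875 × 0.25 = 1.047; SE = √(0.00563 + 0.02358) = 0.171; 0.375/0.171 = 2.19; power = Φ(0.23) = 0.59.
- Separated: n₁′ = 33.3; SE′ = √(0.00563 + 0.03003) = 0.189; 0.50/0.189 = 2.65; power = Φ(0.69) = 0.75.

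| p | observed d, mixed | power, mixed | power, separated |
|---|---|---|---|
| 0% | 0.50 | 0.85 | 0.85 |
| 10% | 0.45 | 0.76 | 0.82 |
| 25% | 0.375 | 0.59 | 0.75 |
| 50% | 0.25 | 0.31 | 0.60 |

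The direction does not depend on the assumed 20%. At p = 25%, power is 0.38 mixed and 0.50 separated if 10% are non-adherent, and 0.71 and 0.87 if 30% are. In each case separation recovers more than the smaller group costs, provided the separated parents really do resemble adherent ones.

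**The case against.** The strongest reply is that the protocol calls this a comparison by adherence and never says the three groups measure hesitancy. Hesitancy has its own instrument, the PACV (Study 1, Vaccine hesitancy), and that score is among the variables compared across the groups. This stands. A reader might infer that the analysis fails to measure vaccine hesitancy; the text does not support that. What remains is narrower: differences between the groups cannot be attributed to parental decisions without qualification.

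Three further strong readings also fail.
- *Adherence is the only behavioural measure.* The PACV has a Behavior sub-domain, and the Sociodemographic list records the parent's own adherence.
- *The intention regression is contaminated too.* That would need pro-vaccine parents of exempt children to answer the intention item negatively. This is conjecture, and Proposed analysis words the criterion as a plan to follow the schedule.
- *Country comparisons are distorted.* Countries are analysed separately, and no between-country test of these groups is planned.

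On size, p may be small. The Introduction attributes missed and late vaccination largely to parents' choice and mentions supply only for some areas. At p = 10% the loss is from 0.50 to 0.45. The wording of the adherence item is in an appendix that is not at hand, so whether an exempt child is recorded as a deviation cannot be checked.

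Replacing the groups outright would also carry a cost. The Introduction notes that parents may cite side effects to justify not vaccinating, so a stated medical reason can itself reflect hesitancy, and participants may leave items blank. This is a sound argument against substitution, but not against a second analysis reported beside the first.

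Finally, a condensed article may leave sensitivity analyses to a fuller plan, and the reported frequencies would give readers some idea of p. That is fair. However, the article does fix both the grouping and the use of the reasons, and it leaves the two unconnected.

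**Conclusion.** The point holds as a limited one. The planned grouping merges two causes of missed vaccination that the protocol itself separates, and the data that could distinguish them are put to no use beyond counting. Under the stated assumption that medical or access cases resemble adherent parents, each mean difference between adherent and non-adherent parents is reduced by the factor (1 − p). The documents give no p, no group sizes and no true difference, so the figures above show a range and are not an estimate. The effect could be slight if p is near 10% and substantial if p approaches 50%.

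The consequence is confined to how one secondary analysis is interpreted. It leaves the PACV as the measure of hesitancy untouched, and no fault in the intention regression has been shown. This is a worthwhile low-cost improvement, not a flaw that undermines Study 1.

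**What to change.** Keep the planned three-group MANOVA and describe it as a comparison by adherence from any cause. Prespecify a second MANOVA in which parents whose stated reason is clearly medical or access-related form a separate category outside the decision contrast. The rules should be:

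- Code the reasons blind to the scale scores, and add access or supply as a named category.
- Leave blank or ambiguous answers in the planned adherence groups.
- Also leave reasons that express perceived vaccine risk or fear of side effects in those groups, since they may be hesitancy itself.
- Report both results for each country, with the number of parents moved, so that p is visible.

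No new data are needed. The cost is some analysis wording, the blinding of the coding already planned, a somewhat smaller non-adherent group in the second analysis, and some misclassification because reasons are self-reported. Showing both analyses lets the reader see how much the conclusion depends on that coding.

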## Abstract

A growing number of parents delay vaccinations or are deciding not to vaccinate their children altogether. This increases the risk of contracting vaccine-preventable diseases and disrupting herd immunity, and also impairs the trust in the capacities of health care systems to protect people. Vaccine hesitancy is related to a range of both psychological and demographic determinants, such as attitudes toward vaccinations, social norms, and trust in science. Our aim is to understand those determinants in parents, because they are a special group in this issue—they act as proxy decision makers for their children, who are unable to decide for themselves. The fact that deciding to vaccinate is a socially forced choice that concerns a child's health makes vaccine-related decisions highly important and involving for parents. This high involvement might lead to parents overemphasizing the potential side effects that they know to be vaccine-related, and by amplifying those, parents are more focused on the potential outcomes of vaccine-related decisions, which can yield specific pattern of the outcome bias. We propose two related studies to investigate factors which promote vaccine hesitancy, protective factors that determine parental vaccination decisions, and outcome bias in parental vaccination intentions. We will explore demographic and psychological factors, and test parental involvement related to vaccine hesitancy using an online battery in a correlation panel design study. The second study is an experimental study, in which we will investigate the moderating role of parents' high involvement in the specific domain of vaccination decision making. We expect that higher involvement among parents, compared to non-parents, will shape the pattern of the proneness to outcome bias. The studies will be conducted across eight countries in Europe and Asia (Finland, Germany, Hong Kong, the Netherlands, Serbia, Slovenia, Spain, and the United Kingdom), rendering findings that will aid with understanding the underlying mechanisms of vaccine hesitancy and paving the way for developing interventions custom-made for parents.

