##### Intention to vaccinate

We will measure parents' willingness to vaccinate their children by their reported intention to vaccinate when presented with the option. To measure this, a single item will be used: “Would you at this time vaccinate your child according to the official vaccination schedule?” A version of this item, with an additional description: “Regardless if you are a parent or not,” was previously used by Stojkovic et al. (2017), who adapted it from the scales by Horne et al. (2015) and Opel et al. (2011). Parents will answer this item on a Likert-type scale ranging from “definitely yes” to “definitely not”. Participants' response to this question will be the dependent variable for this study.

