##### Vaccination scales

To measure the perceived risk of (not) vaccinating may cause in children and society, we will use the vaccination scale developed by Horne et al. (2015). It is a 5-item scale that measures people's general attitude toward the vaccination (i.e., “Vaccinating healthy children helps to protect others by stopping the spread of diseases,” “I plan to vaccinate my children”). This test has proper psychometric features, including a high internal consistency (α = 0.84), and good predictive validity for past and future vaccination behavior, it has not been used in Europe so far.

Furthermore, the Vaccine Conspiracy Belief scale (Shapiro et al., 2016) will be added at this part. This scale contains 10 items, which examine the belief in the conspiracy theory that different entities try to hide the risk of vaccines. This shows the deception rather than the general attitude people have (Shapiro et al., 2016). An example of this item is: “The government is trying to cover up the link between vaccines and autism.” This scale has a very high level of internal consistency (α = 0.94) and is a good predictor of the willingness of parents to vaccinate their children.

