### Anticipated results

The samples of this study will consist of data obtained in eight separate countries. This presents both challenges and possibilities. As some of the factors underlying vaccine hesitancy are context-specific and vary across time and place (Dubé et al., 2014), research in multiple countries is needed to understand vaccine hesitancy more fully on a local level. By analyzing our samples separately, we expect the study to contribute to knowledge on locally relevant factors related to vaccine hesitancy. However, the samples are unlikely to be representative in their respective countries, which limits the reliability of out conclusions on local, but not so much on the general level. Special care will also be taken to make sure that we sample people from all parts of the vaccine-hesitancy spectrum; the call for participants will be posted in different interest groups online along with general population call.

Given the sensitive nature of the topic, it is possible for the participants who participate in the study to have stronger convictions toward vaccines in one way or another, which might further decrease the representativeness of the vaccine hesitancy continuum—we want to include parents with various degrees of their hesitancy and strength of their convictions in order to avoid bipolarization. To decrease the effect of the topic on the motivation to participate, all the communication (e.g., invites, instructions) will be neutral in terms of referencing to potential harms and benefits of vaccination as well as any moral judgements of the decision.

Due to the wide range of phenomena of the present study, we hypothesize to find the following factors to reinforce the intent to vaccinate one's child: trust toward authorities, perceived social and scientific consensus, availability of relevant information, along with previously identified demographic characteristics and open-minded thinking. At the same time, we expect to confirm that vaccine hesitancy, perceived freedom, choice overload, the use of informal sources and susceptibility outcome bias serve as reinforces of delaying or omitting mandatory childhood vaccination. All our hypothesized connections can be seen in Figure 1.

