## Joint discussion

With both studies we aim to investigate and come closer to understanding factors which influence vaccine hesitancy as a possible outcome of the vaccine-related decision-making processes, while focusing on testing the role of the involvement, as a potential underlying factor which skews this decision. Results of Study 1 will provide further insights into factors serving as reinforcements of the delay and omission of vaccination but also factors serving as reinforcements of the intention to vaccinate, as well as their interrelatedness. The results will provide insights into the construct of vaccine hesitancy that is currently lacking different stakeholders combating dropping immunization rates.

Moreover, if the Study 2 yields results consistent with our hypotheses, we will gain valuable proof that in terms of the extent and lengths of the decision-making processes regarding vaccination of their children, parents are indeed a special group, different from people without children, who do not have to face such dilemmas, and are therefore susceptible to different cognitive obstacles to reaching a decision to vaccinate.

With such knowledge it would be possible to draft interventions custom-made for parents aimed toward undermining their vaccine hesitancy by establishing better communication channels and better, more effective formation of relevant, informative and non-patronizing messages, addressing their personal dilemmas and fears with respect and understanding. Parents might not be afraid of vaccine-preventable diseases, but it seems they are afraid of vaccines – and the burden of the immunity of our herd lies on their shoulders.

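### Study 1's mediation test uses variables measured once in one sitting, so it cannot tell the hypothesised order from a reversed chain or from a mediator that causes both, yet the article announces reinforcing factors

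*Protocol article*

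**What the plan says.** The Proposed analysis of Study 1 commits to a specific test: "We will test the proposed model of mediation (Figure 1) using regression analysis and compare it to a more complicated model". The more complicated model is the same one with involvement added. No alternative ordering is named as a comparator.

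Under Design, sample, and procedure, participants give demographic data and "complete a battery of vaccination- and decision-making-related questions, with a total of 115 items". On duration the article says "The study will take ~25 min to complete". No second wave is described. The outcome is one item of that battery; the section on intention to vaccinate states "Participants' response to this question will be the dependent variable for this study". The abstract nevertheless describes Study 1 as "using an online battery in a correlation panel design study".

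The wording on what Study 1 will show is directional. Its Introduction sets out to explore factors that influence hesitancy. Anticipated results says "we hypothesize to find the following factors to reinforce the intent to vaccinate one's child" and expects to confirm a second set that reinforces delay or omission. The Joint discussion says that Study 1 will give insight into "factors serving as reinforcements of the delay and omission of vaccination". The limitations in Anticipated results concern representativeness and self-selection. None concerns direction or common causes.

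**The concern.** A mediation model asserts an order: the predictor acts on the mediator, which acts on intention. Regression on simultaneous measurements can show that the associations are compatible with that order. It cannot show that the order is right.

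Reversal is a live possibility here. Participants have a child under 12, and past adherence to the schedule is collected, so many will already have vaccinated or refused. The freedom and choice-overload example items are in the past tense and describe a decision already taken, yet these scales serve as predictors of present intention. The vaccination attitude scale, also a predictor, contains the item "I plan to vaccinate my children", which is close to the outcome itself.

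What is at stake is the use of the result. The Joint discussion carries the findings forward to interventions designed for parents. If trust or perceived consensus partly follows from the decision, or shares a cause with it, an intervention on that factor need not change intention.

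**Working it through.** **Inputs from the article.** Minimum 222 participants per country; effect size 0.15; 20 predictors in a multiple regression; each country analysed separately; one administration. **Assumed, not in the article:** standardised path sizes of 0.2, 0.3 and 0.4, two-sided alpha of 0.05, and joint significance as the test of mediation.

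**Step 1. The article's own figure.** Take 0.15 as Cohen's f² and test R² against zero with 20 and 222 − 21 = 201 degrees of freedom. The noncentrality is 0.15 × 222 = 33.3. At alpha 0.05 the power is 0.951, and 222 is the smallest sample that reaches 95%. Alpha and power are not stated, but this pair reproduces 222 exactly. The figure powers the overall regression. It has no bearing on direction, and a larger sample would not help.

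**Step 2. What the structures imply.** Let X be the predictor, M the mediator, Y intention, and let both paths equal p. Three structures are compared: X→M→Y, Y→M→X, and M causing both X and Y. Each gives

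- r(X,M) = p
- r(M,Y) = p
- r(X,Y) = p × p = p²

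The test uses path a = r(X,M) = p, and path b, the coefficient of M in the regression of Y on X and M:

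b = [r(M,Y) − r(X,M) r(X,Y)] / [1 − r(X,M)²] = (p − p³)/(1 − p²) = p

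All three structures therefore give the same a and the same b. With X, M and Y all in the model, the forward and reversed versions also have the same likelihood (differences below 1e-12 in simulation), so fit cannot choose between them.

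**Step 3. Structures that do differ.**

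- Intention causes both X and M: r(X,M) = p², r(M,Y) = r(X,Y) = p. Then a = p² and b = (p − p³)/(1 − p⁴) = p/(1 + p²). At p = 0.3, a = 0.09 and b = 0.3/1.09 = 0.275. The small a makes the test fail often.
- X causes both M and Y: r(X,M) = r(X,Y) = p, r(M,Y) = p². Then b = (p² − p²)/(1 − p²) = 0. The test passes at about alpha at most, although all three variables are correlated.

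**Step 4. Pass rates by simulation, n = 222.** Both a and b must be significant at 0.05.

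| True structure | p = 0.2 | p = 0.3 | p = 0.4 |
|---|---|---|---|
| X→M→Y (hypothesised) | 71% | 99% | 100% |
| Y→M→X (reversed) | 71% | 99% | 100% |
| M causes X and Y | 72% | 99% | 100% |
| Y causes X and M | 8% | 27% | 66% |
| X causes M and Y | about 5% | about 5% | about 5% |

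An unmeasured cause of all three variables, with no paths among them and pairwise correlations of 0.3, passes in 93% of samples (99% at correlations of 0.4). With three unrelated variables the test passes in 0.2% of samples, so the test itself is not faulty.

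**Step 5. The planned comparator.** The article compares Figure 1 only with Figure 1 plus involvement. Involvement is measured in the same battery. The comparison asks whether a further factor adds something; it does not set one ordering against another.

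**The case against.** The strongest reply is that Study 1 presents itself as correlational. Its heading speaks of correlates, the abstract uses the word correlation, the overview of the two studies says variables will be tested for their connection with differences among parents, and the analysis section speaks of predictive power. The reinforcing factors in Anticipated results are introduced as a hypothesis. The general aim of finding factors that affect decisions covers both studies, and Study 2 is experimental. All of this is fair, and that general aim should not be held against Study 1 alone. It does not remove the problem. Anticipated results also expects confirmation, the Joint discussion attributes reinforcing factors to Study 1, and no caveat on direction is given. Study 2 varies domain, involvement, protagonist and outcome, not trust, consensus, freedom or overload, so it cannot supply the missing direction.

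A second reply is that Figure 1 is not available, that several relations set out in the text are moderation, and that paths from age or number of children can hardly run backwards. This stands and limits the scope of the point.

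A reader might also infer that the test will confirm Figure 1 whenever the variables are correlated, including whenever parents adjust several beliefs to a decision already made. The working does not support that. If intention drives both predictor and mediator, the pass rate is 8% to 66% over the assumed paths, and with the predictor as common cause it stays near 5%.

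**Conclusion.** The point holds in a limited form. For psychological variables measured in the same sitting, a significant indirect effect is equally expected under the hypothesised chain, the reversed chain and a mediator that causes both. It is also likely under an unmeasured common cause of all three. Study 1 can therefore report indirect association, but it cannot support statements that a factor influences or reinforces intention, delay or omission. The equality of the first three structures is algebraic and does not depend on the path size. The percentages do depend on the assumed paths, on n = 222 and on joint significance as the test.

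Two stronger readings are not supported. The test does not pass for every correlated set of variables. Nor is the whole of Figure 1 shown to be reversible: fixed demographics are largely exempt, and the share of affected paths cannot be judged without the figure. The word panel in the abstract has no repeated measurement behind it; no planned analysis relies on a second wave, so this is a labelling error. The data remain useful. What changes is the conclusion that may be drawn from them.

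**What to change.** - **Study 1, Proposed analysis:** describe the Figure 1 analysis as a test of indirect association.
- **Abstract:** replace panel with cross-sectional.
- **Study 1 Introduction, Anticipated results and Joint discussion:** limit Study 1's conclusions to association, and add one sentence saying that neither direction nor common causes can be resolved from a single administration.
- **Optional:** report the reversed-order model beside Figure 1, labelled as an illustration that the two are equivalent. It does not discriminate between them.
- **Not recommended as a remedy:** repeating the analysis within past-adherence groups. This conditions on a variable close to the outcome and splits a minimum of 222 into three levels. If done at all, label it exploratory.

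The cost is wording, plus one extra model per country if the optional report is taken up. No new data are needed. The downside is a weaker causal claim from Study 1.
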